#### **6.4 Randomisation**

This is a randomised, single-blind study. When the informed consent and assent forms are signed and the eligibility criteria are confirmed, the subject will be randomized to intervention or control group at a 1:1 allocation ratio, giving approximately 86 subjects in each group. Balanced treatment assignments will be achieved using permuted block randomisation, stratified by gender and age, across one study site. The stratification factor for age will be categorized into two groups, aged 6-9 years old and aged 10-12 years old. Block size will be determined by the study statistician and will not be made known to the clinical investigators or site personnel. The randomization procedure, done after obtaining consent, assent and CDISC results at Week 0, will assign a unique “subject number” to each child.

Implementation of randomisation will be carried out via a web-based program at SCRI. Authorized study centre personnel will randomise the patient via a password-protected internet web site. The randomisation system will then determine the treatment arm and provide the subject number to be used for the patient. The site monitor/CRA will be informed immediately in the event that the web randomization is not successful. Back-up randomisation envelopes will be provided to the site in case of internet failure.

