### **2.1.2 Primary Endpoint**

The primary outcome of this study will be the change in the inattentive score on the ADHD Rating Scale as rated by the clinicians from week 1 to week 8.

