## 4. Trial Schedule

During Pre-Screening, the parent/legal guardian will complete the structured interview, CDISC.

Once the diagnosis of ADHD (inattentive/combined subtype) has been made, the parent/legal guardian will complete the following questionnaires during the baseline stage (Week 1):

a. ADHD Rating Scale

b. Child Behavior Checklist

If the child has ever been placed in the school's Learning Support Program and/or is currently failing a subject, he/she will be screened using the Kaufman Brief Intelligence Test.

The assessment schedule is summarized in Table 1 section 6.6.

Once the diagnosis of ADHD has been made, the following assessments will be completed by different informants:

CLINICIAN:

1. ADHD Rating Scale (ADHD- RS)
2. Clinical Global Assessment Scale (CGAS)
3. Clinical Global Impression - Severity Scale (CGI-S)
4. Clinical Global Impression – Improvement Scale (CGI-I)
5. Pediatric Adverse Event Rating Scale (PAERS) from week 8 onwards as there will be nothing to report at the first session.

PARENT:

1. ADHD Rating Scale (ADHD-RS)
2. Child Behavior Checklist (CBCL)

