## 5. Study Design

Our hypothesis is that children with ADHD receiving treatment with the BCI-based training will improve to a greater extent than the control group. This will be organized as a prospective single blind randomized clinical trial (clinicians blinded to subjects treatment arm), with the comparator arm being a

wait-list control. All subjects will eventually receive the BCI intervention but subjects in the control arm will not receive it until week 9.

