### **6.3 Briefing session for all potential subjects**

During briefing sessions, the research team will provide an overview of ADHD and a demonstration of the BCI study will be conducted for parents to view. It will be highlighted that medication and psychosocial treatment represent current evidence-based treatment for this disorder. The BCI study will be presented as an alternative form of treatment that is being investigated in this study and parents will have ample time and opportunity to choose the treatment of preference. At the end of each briefing, parents will be provided with participant information sheets to take home for further consideration of participation.

After the briefings, parents will be contacted within one to two weeks to give all subjects sufficient time to contemplate and ask any queries pertaining to the study. If the parents indicate interest, a session will then be arranged for informed consent to be taken. Informed consent will be obtained from the parents, and assent from the subjects, prior to any form of assessment or intervention as part of the study. The blinded clinician will contact the child's school teacher(s) and obtain feedback about the child's behavior in school at various time points. This will be made known to parents during the briefing session. All trial-related procedures will only take place after informed consent has been obtained. A baseline assessment will be done to determine the child's eligibility for the study.

In the event that the child is eligible but the parents/legal guardians choose not to participate in the study, the parents/legal guardians will be offered an option to have the child be followed-up at the CGC.

Participation is strictly voluntary and at any point if the subject wishes to drop-out, he/she will not be restricted or punished for it.

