#### **6.5 Blinding**

Clinicians conducting the study assessments will be blinded to the study arm. Teachers who will be providing feedback to the clinicians will be blinded as well. Study Investigators, study personnel (including the SCRI study team), parents and subjects are not blinded in this study. Parents and subjects will be advised regularly not to inform the clinicians or teachers to which group the subjects are assigned.

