| Clinical Global Impression - Improvement Scale                            | Group 1     |                     | XX       | XX           |              | X       |             | X         |         |
|                                                                           | Group 2     |                     |          |              | X            |         | X           |           | X       |
| ADHD Rating Scale                                                         | Group 1     |                     | XX       | XX           |              | X       |             | X         |         |
|                                                                           | Group 2     |                     |          |              | X            |         | X           |           | X       |
| Pediatric Adverse Event Rating Scale (PAERS)                              | Group 1     |                     |          | X            |              | X       |             | X         |         |
|                                                                           | Group 2     |                     |          |              | X            |         | X           |           | X       |

NB: All assessment visits will be completed accordingly to the assessment week within the window period of +/- 5 working days.

Figure 1: Study Visit and Procedure for Both Groups

**Appendix A****Schedule 1: Gantt schedule of Phase 2 overall study design and timelines for intervention & control groups.**[figure not shown]**Assessments for both intervention and control group**

| Week 0                      | Week 1
(+/- 5 work days)   | Week 8
(+/- 5 work days)                              | Week 16
(+/- 5 work days)  | Week 20 (Intervention)
Week 28 (Control)
(+/- 5 work days) | Week 24 (Intervention)
Week 32 (Control)
(+/- 5 work days) |
|------------------------------------|---------------------------------------------|------------------------------------------------------------------------|---------------------------------------------|-----------------------------------------------------------------------------------------------------|-----------------------------------------------------------------------------------------------------|

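### Randomising at Week 0 puts every Week 1 baseline rating after allocation, with families unblinded, and the visit window is not tied to the first BCI session

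*Protocol*

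**What the plan says.** **Order of events.** Protocol section 6.4 allocates at Week 0: "The randomization procedure, done after obtaining consent, assent and CDISC results at Week 0, will assign a unique" subject number to each child. Table 1 and the assessment schedule in section 6.6 also put randomisation at pre-screening. The clinician and parent ADHD-RS, CBCL, C-GAS, CGI and CPT baselines are all at Week 1 (sections 4 and 6.6). The primary endpoint in section 2.1.2 is "the change in the inattentive score on the ADHD Rating Scale as rated by the clinicians from week 1 to week 8". Section 11.2.3 compares these changes with a two-sample t test, and section 11.2.1 defines the ITT set as everyone randomised.

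**Blinding.** The trial is single blind. Section 6.5 blinds the assessing clinicians and the teachers who give them feedback. Investigators and study personnel are not blinded, and "parents and subjects are not blinded in this study". Families are to be reminded regularly not to reveal the arm.

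**Windows.** The note to Table 1 reads: "All assessment visits will be completed accordingly to the assessment week within the window period of +/- 5 working days". Section 5.1 gives the intervention arm 24 sessions over 8 weeks. Section 5 says that "subjects in the control arm will not receive it until week 9". The control arm's Week 8 rating is labelled Pre-Tx in section 6.6 and pre-BCI in section 11.2.3.

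**Eligibility.** Section 6.3 says: "A baseline assessment will be done to determine the child's eligibility for the study". Section 6.4 requires eligibility to be confirmed before randomisation.

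**The concern.** The starting value of a change score should be fixed before anyone can know the arm. Here it is measured after allocation, in a trial where the family is told the arm at some point, where parents complete two of the baseline scales themselves, and where a parent or guardian accompanies the child to every clinic visit (section 12.1). Any difference that knowledge of the arm creates in the baseline enters the unadjusted change score in full.

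The order also opens a gap between joining the ITT set and having a baseline. A family that leaves in that gap, for instance on learning that it is on the wait-list, counts as randomised but has no change score.

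The window raises a separate question. A period of 5 working days after Week 1 or Week 8 is a full training week, and nothing says that the rating must come before the first session. An intervention baseline could therefore include some training, and so could a control rating that is meant to be untreated.

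**Working it through.** **1. The plan's own figure.** Inputs from sections 11.1 and 11.2.1: effect 0.5 SD, power 80%, two-sided 5%, 20% loss.

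- Normal formula: n = 2(1.960 + 0.842)² / 0.5² = 62.8, so 63 per group; 63/0.8 gives 79.
- Exact t test: 64 per group; 64/0.8 = 80.

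The stated figure of about 80 is reproduced. Below, 64 evaluable per group is the planning case. The 86 per group to be enrolled, less 20%, leaves 68.

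**2. How a baseline shift enters the estimate.** The estimate is (Week 8 − Week 1 in intervention) − (Week 8 − Week 1 in control). If knowledge of the arm moves the Week 1 means apart by b, with Week 8 unaffected, the estimate moves by b in size. Its sign depends on which families shift their reports and in which direction, which the protocol cannot tell us.

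**3. Type I error under an assumed shift b (in SD of change).** The standard error of the standardised difference is √(2/64) = 0.177. The two-sided rejection rate with no true effect is 1 − Φ(1.960 − b/0.177) + Φ(−1.960 − b/0.177).

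| Assumed b | Share of planned 0.5 SD | Type I error, 64 per group | 68 per group |
|---|---|---|---|
| 0.05 | 10% | 5.9% | 6.0% |
| 0.10 | 20% | 8.7% | 9.0% |
| 0.20 | 40% | 20.5% | 21.5% |

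The protocol gives no value for b.

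**4. What the window permits.** 24 sessions / 8 weeks = 3 per week. Five working days is one working week, so about 3 sessions, or 3/24 = 12.5% of the course. The intervention arm's Week 8 rating is labelled Post-Tx, so an 8-week course must start in or about week 1, although no start day is given. For controls, the Week 8 window runs into week 9, when training begins.

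**5. Power if ratings slip.** Assume that benefit accrues linearly over the 24 sessions. A late intervention baseline removes part of that arm's change; a late control rating adds benefit to the control arm. If a share p of the children in the relevant arm is late by 3 sessions, the effect is 0.5(1 − p × 3/24) for one end and 0.5(1 − 2p × 3/24) for both. Power is Φ(d/√(2/n) − 1.960).

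| Scenario | Effect d | Power, n = 64 | Power, n = 68 |
|---|---|---|---|
| No slips | 0.500 | 80.7% | 83.0% |
| 10% late, both ends | 0.487 | 78.7% | 81.1% |
| 25% late, both ends | 0.469 | 75.5% | 78.0% |
| All late, one end | 0.438 | 69.7% | 72.3% |
| All late, both ends | 0.375 | 56.4% | 59.0% |

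The last two rows are bounds for a 3-session slip, not expectations. With no true effect, sessions change nothing, so slips cannot raise type I error.

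**The case against.** The strongest reply is that the primary rater is blinded. A reader who sees unblinded families might call the trial open-label and treat the primary baseline as directly exposed. The protocol does not support that: knowledge of the arm can reach the clinician's score only through what families report, or through accidental unblinding. A shift of 0.2 SD may well be too large for a blinded rater. Nor does the protocol say when families are told their arm; that they may know by Week 1 is an inference from allocation at Week 0, the absence of blinding and a training start in or about week 1. This limits the size of the problem for the primary endpoint. It does not limit it for the parent-rated secondary endpoints.

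The intent on timing is also clear. Table 1 sets Baseline in a column before treatment, and the control's Week 8 rating is labelled as preceding treatment. That makes mistimed ratings less likely, but it does not override a window stated for all assessment visits.

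Three other stronger readings fail:

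- **Five sessions before a rating (5/24 = 20.8%).** That weekly rate is for making up missed sessions, and in the first training week there is ordinarily nothing to make up.
- **A flat contradiction on eligibility.** No criterion in sections 3.1 and 3.2 uses a Week 1 score, so the baseline assessment in section 6.3 can be read as the pre-screening C-DISC and selected KBIT-2. The wording is loose because baseline means Week 1 elsewhere.
- **An ITT analysis that cannot be done.** Handling of missing baselines may be set out in an analysis plan that is not shown, and section 11.1 allows for 20% losses. What stands is that the chosen order creates such cases without need.

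**Conclusion.** The point holds as a modest but avoidable weakness. All baselines follow allocation, and nothing stops the Week 1 rating, or the control's Week 8 rating, from coming after the first session.

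The two parts act differently and should not be added together. Knowledge of the arm could move the estimate in either direction and is the only one of the two that could inflate it. A reader might infer that the window also adds false positives; it does not, because late ratings only dilute the group difference and cost power. Nor can the two be relied on to cancel.

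The sizes are conditional. Type I error of about 6%, 9% or 20% rests on assumed shifts of 0.05, 0.1 or 0.2 SD. The fall in power from about 81% to about 76% rests on linear benefit and on a quarter of children being late at each end; with 68 evaluable per group it is 83% to 78%. The protocol gives neither the shift nor the share affected, nor the number who might leave between Week 0 and Week 1. The case for acting is that later analysis cannot fully repair a baseline taken after allocation or after training has begun, while prevention is cheap.

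**What to change.** - **Section 6.4, Table 1 and the assessment schedule:** randomise only after the Week 1 baseline ratings are completed and entered, as the last step of that visit.
- **Note to Table 1:** state that the Week 1 rating, and the control arm's Week 8 rating, must each precede that child's first BCI session, and that the window ends there.
- **Section 6.3:** say that eligibility rests on the pre-screening assessments.

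The cost is a reordering of steps in the web randomisation, a schedule edit and slightly less lead time to book the first training session. No visit is added and the sample size is unchanged. The change protects the baseline only: the same unblinded families remain informants at Week 8, so expectation effects on those ratings remain.

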#### **6.5 Blinding**

Clinicians conducting the study assessments will be blinded to the study arm. Teachers who will be providing feedback to the clinicians will be blinded as well. Study Investigators, study personnel (including the SCRI study team), parents and subjects are not blinded in this study. Parents and subjects will be advised regularly not to inform the clinicians or teachers to which group the subjects are assigned.

## 6.6 Study Visits and Procedure

**Table 1: Study Schedule [Phase 2]**

\* Note: Group 1 = Intervention group  
Group 2 = Control group

|                                                                           |             | Pre-Study Screening | Baseline | Treatment G1 | Boosters G1  |         | Boosters G2 | Follow-Up |         |
|---------------------------------------------------------------------------|-------------|---------------------|----------|--------------|--------------|---------|-------------|-----------|---------|
|                                                                           |             |                     |          | Control G2   | Treatment G2 |         |             |           |         |
| Week                                                                      |             | NIL                 | Week 1   | Week 8       | Week 16      | Week 20 | Week 28     | Week 24   | Week 32 |
| Duration of Visit                                                         |             | 2 hours             | 1 hour   | 75 min       | 30 min       | 60 min  | 60 min      | 30 min    | 30 min  |
| Informed Consent                                                          | Both groups | XX                  |          |              |              |         |             |           |         |
| Computerised Diagnostic Interview Schedule for Children [C-DISC] (Parent) | Group 1     | XX                  |          |              |              |         |             |           |         |
|                                                                           | Group 2     |                     |          |              |              |         |             |           |         |
| Conner's Continuous Performance Test II [CPT-II] (Child)                  | Group 1     |                     | XX       | XX           |              | X       |             | X         |         |
|                                                                           | Group 2     |                     |          |              | X            |         | X           |           | X       |
| Kaufman Brief Intelligent Test [KBIT-2] (Child) [Selected]                | Group 1     |                     |          |              |              |         |             |           |         |
|                                                                           | Group 2     | XX                  |          |              |              |         |             |           |         |
| Randomisation                                                             | Both groups | XX                  |          |              |              |         |             |           |         |
| Parent Questionnaire                                                      |             |                     |          |              |              |         |             |           |         |
| Child Behaviour Checklist [CBCL] (113 items)                              | Group 1     |                     | XX       | XX           |              | X       |             | X         |         |
|                                                                           | Group 2     |                     |          |              | X            |         | X           |           | X       |
| ADHD Rating Scale                                                         | Group 1     |                     | XX       | XX           |              | X       |             | X         |         |
|                                                                           | Group 2     |                     |          |              | X            |         | X           |           | X       |
| Clinician Questionnaire                                                   |             |                     |          |              |              |         |             |           |         |
| Clinical Global Assessment Scale                                          | Group 1     |                     | XX       | XX           |              | X       |             | X         |         |
|                                                                           | Group 2     |                     |          |              | X            |         | X           |           | X       |
| Clinical Global Impression - Severity Scale                               | Group 1     |                     | XX       | XX           |              | X       |             | X         |         |
|                                                                           | Group 2     |                     |          |              | X            |         | X           |           | X       |
| Clinical Global Impression - Improvement Scale                            | Group 1     |                     | XX       | XX           |              | X       |             | X         |         |
|                                                                           | Group 2     |                     |          |              | X            |         | X           |           | X       |
| ADHD Rating Scale                                                         | Group 1     |                     | XX       | XX           |              | X       |             | X         |         |
|                                                                           | Group 2     |                     |          |              | X            |         | X           |           | X       |
| Pediatric Adverse Event Rating Scale (PAERS)                              | Group 1     |                     |          | X            |              | X       |             | X         |         |
|                                                                           | Group 2     |                     |          |              | X            |         | X           |           | X       |

NB: All assessment visits will be completed accordingly to the assessment week within the window period of +/- 5 working days.

Figure 1: Study Visit and Procedure for Both Groups

**Appendix A****Schedule 1: Gantt schedule of Phase 2 overall study design and timelines for intervention & control groups.**[figure not shown]**Assessments for both intervention and control group**

| Week 0                      | Week 1
(+/- 5 work days)   | Week 8
(+/- 5 work days)                              | Week 16
(+/- 5 work days)  | Week 20 (Intervention)
Week 28 (Control)
(+/- 5 work days) | Week 24 (Intervention)
Week 32 (Control)
(+/- 5 work days) |
|------------------------------------|---------------------------------------------|------------------------------------------------------------------------|---------------------------------------------|-----------------------------------------------------------------------------------------------------|-----------------------------------------------------------------------------------------------------|
| Pre-screening               | Baseline                             | Post-Tx (Intervention)
Pre-Tx (control) | Post-Tx (control)             | Post-booster                                                                                 | Follow-up                                                                                    |
| Parents:
C-DISC          | Parents:
ADHD-RS / CBCL           | Parents:
ADHD-RS / CBCL                                      | Parents:
ADHD-RS / CBCL           | Parents:
ADHD-RS / CBCL                                                                   | Parents:
ADHD-RS / CBCL                                                                   |
| Child:
K-BIT2 (selected) | Clinician:
ADHD-RS
C-GAS / CGI | Clinician:
ADHD-RS
C-GAS / CGI                            | Clinician:
ADHD-RS
C-GAS / CGI | Clinician:
ADHD-RS
C-GAS / CGI                                                         | Clinician:
ADHD-RS
C-GAS / CGI                                                         |
| Randomisation               | Child:
CPT                        | Child:
CPT                                                   | Child:
CPT                        | Child:
CPT                                                                                | Child:
CPT                                                                                |

